### Trial design {8}

This study will be an open-label, superiority, three-arm individual randomized controlled diagnostic trial to evaluate a new algorithm including two-step malaria RDT and PoC tests for bacterial infections: (1) control arm, (2) RDT decisional algorithm (RDT-DA) arm, and (3) e-algorithm arm.

In the 3 arms, healthcare workers will be trained to perform properly the clinical examination.In the control arm, the diagnostic and management will be based on IMCI and guidelines of diagnostic and treatment (GDT). The management of the participant will be only supported by a one-step malaria RDT, rolled-out by the MoH for malaria management in primary health facilities. The diagnosis and prescription will be left to the discretion of the healthcare workers, based on the Integrated Management of Childhood Illnesses (IMCI) and GDT.In the RDT-DA arm, the presumptive diagnostic will base on IMCI and guidelines of diagnostic and treatment (GDT). This presumptive diagnostic will be supported by biomarkers PoC diagnostic tools (CRP, WBC and urine dipstick), pathogen-specific antigen RDT (two step malaria RDT and bacteria), and pulse oximetry to determine if a prescription of antibiotic is needed. However, in this arm, the diagnosis and prescription will be left to the discretion of the healthcare workers, based on clinical examination and PoC test results.In the e-Algorithm arm, the clinical examination will be supported by the two-step malaria RDT and the PoC tests for bacterial infections to determine if a prescription of antibiotic is needed. However, in this arm, the clinical evidence and the results of malaria two-step RDT and the PoC tests for bacterial infections will be digitalized to guide diagnostic and propose treatment. After the properly completion of the e-Algorithm, the final diagnosis will be done by the algorithm as well as the prescriptions (antibiotics and antimalarials mainly).

In the decisional algorithm arms (RDT-DA) and e-Algorithm arms, the PoC tests will be done by trained nurses.

In the 3 arms, the study CRFs (case report forms) of data collection will be digitalized on tablets for an electronic data collection.

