#### Specific objectives

Estimate the cost of the proposed algorithm in the health facilities of the Nanoro health district;Estimate the costs of routine practices used in health facilities in the Nanoro health district;Calculate the incremental cost-effectiveness ratio;Determine the most cost-effective algorithm.

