#### Methodology

*Type of survey*: A prospective study will be implemented to evaluate the cost effectiveness of the proposed algorithm in comparison with the routine algorithm in health facilities.

*Study sites*: The study sites are those of the e-MANIC study, namely the health centers of Siglé and Pella.

*Study perspective*: In Burkina Faso, children under 5 years of age are part of the UHC policy. So, all costs related to their healthcare are free of charge for parents/guardians. For that, we assumed that all costs were borne by the health facility, even those borne by the government such as salaries of health staff in each group (control and intervention). In short, our study perspective will be that of the care provider.

*Cost estimate*: To compare a medical intervention with another with the same objective, the most appropriate type of economic evaluation is a cost-effectiveness study. The two algorithms have the same efficiency indicator, namely the rate of cure and prescription of antimicrobials (antimalarials and antibiotics).

The approach taken for cost estimation is that of Larson et al. [22] which was used in a syphilis detection project in Zambia.

This approach proceeded by the inclusion of six parameters which are (1) the cost of the material per test, (2) staff time per test, (3) salary costs per test, (4) daily start-up and quality control costs, (5) cost of equipment, and (6) the average number of tests performed per day. Taking into account the type of algorithm used, we will make a selection of the parameters to include. Already, the costs of equipment such as scales, stethoscope, measuring tape, table, and chair were excluded because their costs are amortized. Additionally, building costs such as examination room, waiting room were also excluded for the same reason. The costs of electricity and the time-motion method will also be used to estimate the time spent to implement the diagnostic algorithms.

*Sample size*: All health facilities in the e-MANIC diagnostic study will be invited to participate in this ancillary study. Health workers from the study and health centers participating in the study will also be invited to participate in the study through interviews to assess the acceptability of the proposed algorithm.

*Collection tools and techniques*: Data collection will consist of observing consultations on the sites and administering a questionnaire based on an interview guide.

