The observation technique will be used for the study of time motion. It will make it possible to estimate the time taken for a consultation using the proposed algorithm and in the routine. An observation grid will be developed for this purpose.

The oral interview technique will be used to collect the perceptions of health workers on the acceptability of the algorithm. To this end, individual interviews will be conducted. In addition, a questionnaire will be developed to collect information about the health facility.

*Data analysis*: Quantitative data processing software such as SPSS (Statistical Package for the Social Sciences) and Excel will be used. A data analysis plan will be developed.

The major costs of the different algorithms will be highlighted. The healing rates of each algorithm will be estimated and will serve as an efficiency comparator. The incremental ratio will be calculated according to the following formula:$$\frac{\mathrm{cure}\ \mathrm{rate}\ \mathrm{of}\ \mathrm{the}\ \mathrm{proposed}\ \mathrm{algorithm}-\mathrm{cure}\ \mathrm{rate}\ \mathrm{of}\ \mathrm{the}\ \mathrm{routine}\ \mathrm{algorithm}}{\mathrm{cost}\ \mathrm{of}\ \mathrm{the}\ \mathrm{proposed}\ \mathrm{algorithm}-\mathrm{costs}\ \mathrm{of}\ \mathrm{the}\ \mathrm{routine}\ \mathrm{algorithm}}$$

The data collected through the individual interviews will be transcribed. A transcription coding grid will be developed. A thematic analysis will follow.

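### The economic evaluation prints its incremental ratio as cure difference over cost difference, the reciprocal of the ICER it promises, and its effect measure, contrasts and cost inputs do not match its stated aims

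*Protocol article*

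**What the plan says.** The aims are under Specific objectives of the health economic survey: "Calculate the incremental cost-effectiveness ratio;Determine the most cost-effective algorithm".

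Under Methodology, Data analysis, the ratio is introduced by "The incremental ratio will be calculated according to the following formula". The displayed formula has the cure rate under the proposed algorithm minus that under routine as numerator, and the corresponding difference in cost as denominator. The effect measure is stated just before it: "The healing rates of each algorithm will be estimated and will serve as an efficiency comparator".

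Under Methodology, Cost estimate, the effect is described differently: "The two algorithms have the same efficiency indicator, namely the rate of cure and prescription of antimicrobials (antimalarials and antibiotics"). The comparison set for the economic study is to "evaluate the cost effectiveness of the proposed algorithm in comparison with the routine algorithm in health facilities". The trial has three arms: "1) control arm, (2) RDT decisional algorithm (RDT-DA) arm, and (3) e-algorithm arm".

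The costing approach proceeds by "inclusion of six parameters which are (1) the cost of the material per test, (2) staff time per test, (3) salary costs per test", followed by daily start-up and quality control, equipment, and the average daily number of tests. Electricity and a time-motion measurement of consultation time are added. The perspective is the care provider's, with every cost taken to fall on the facility. The Discussion expects the project to lower what treating a fever episode costs by reducing inappropriate antibiotic use.

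**The concern.** An ICER is the extra cost divided by the extra effect. The printed expression is the extra effect divided by the extra cost. When both differences are positive, smaller is better for an ICER and larger is better for the printed ratio. Someone who takes the result at its announced name would read the preference backwards, and the article says its results are meant to inform policy.

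Three further mismatches affect what the ratio can answer:

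- It leaves out antimicrobial prescription, which the same section names as part of the effect and which is a primary trial outcome.
- It gives one contrast, while choosing the most cost-effective algorithm among three strategies also needs the step from one intervention arm to the other.
- The named cost inputs cover delivering tests. If medicines stay out, the treatment saving expected in the Discussion cannot show up in the cost difference.

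**Working it through.** The article gives no unit costs and no expected cure difference, so there is no cost-effectiveness figure to reproduce. All costs (arbitrary units per child) and cure differences below are assumptions. ΔE is the difference in cure rate and ΔC the difference in cost.

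**1. Direction of the ratio**

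- As printed: ΔE/ΔC. As named under Specific objectives: ΔC/ΔE.
- With ΔE = 0.02 and ΔC = 5: printed 0.02/5 = 0.004; ICER 5/0.02 = 250 units per extra cure.
- Over ΔE from 0.01 to 0.05 and ΔC from 2 to 8: printed from 0.01/8 = 0.00125 to 0.05/2 = 0.025; ICER from 2/0.05 = 40 to 8/0.01 = 800.

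**2. Contrasts**

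Take, against control, RDT-DA with ΔE = 0.02 and ΔC = 4, and the e-algorithm with ΔE = 0.03 and ΔC = 8.

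- RDT-DA against control: 4/0.02 = 200.
- e-algorithm against control: 8/0.03 = 267.
- e-algorithm against RDT-DA: (8 − 4)/(0.03 − 0.02) = 400.

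The two ratios against control look close. The price of each further cure gained by moving from RDT-DA to the e-algorithm is twice the first ratio, and comparisons with routine alone do not display it.

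**3. Effect measure**

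The Sample size section gives 62.63% of febrile children prescribed an antibiotic in 2018. Its wording of the expected reduction can be read in three ways:

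| Reading | Courses averted per 100 children | Per arm of 392 |
|---|---|---|
| 20% relative fall | 62.63 × 0.20 = 12.5 | 49 |
| Fall of 20 points | 20.0 | 78 |
| Fall to 20% | 62.63 − 20 = 42.6 | 167 |

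None of these enters a ratio built on cure alone. At ΔC = 4, the cost per antibiotic prescription averted would be 4/0.1253 = 31.9, 4/0.20 = 20.0 or 4/0.4263 = 9.4 units.

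**4. Medicines**

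Let c be the price of an antibiotic course and a the courses averted per child, with nothing substituted and no other cost changing. Then ΔC = 4 − c × a, with ΔE = 0.02.

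- c = 1, a = 0.1253: ΔC = 3.87, ICER = 194.
- c = 5, a = 0.20: ΔC = 3.00, ICER = 150.
- c = 10, a = 0.4263: ΔC = −0.26, ratio = −13, meaning more cures at lower cost.
- Medicines left out: ΔC = 4, ICER = 200.

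In this range the effect of counting courses runs from negligible to a change of sign. Substituted medicines or additional unscheduled visits would push ΔC the other way.

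**The case against.** The strongest reply is about weight. Methodology calls the economic work ancillary, and cost-effectiveness is neither a primary nor a secondary trial outcome. The formula spells out its numerator and denominator, so a careful reader can see its direction, and inverting it needs no new data. All of that stands. It limits the consequence but does not make the printed expression the measure named under Specific objectives, and nowhere does the article say that effect per unit cost is intended.

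Four stronger readings are tempting, and the article does not support them:

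- **That one intervention arm is ignored or the two are pooled.** The section on the choice of comparators uses the term proposed algorithm for both interventions, and the economic sections refer to each algorithm and to the most cost-effective one. The formula may be a template applied to each arm. What remains is that the contrasts are unstated, the text speaks of two algorithms, and no e-algorithm against RDT-DA step appears.
- **That medicines are excluded, so the algorithm will look too expensive.** Only three of the six parameters are worded as per test, one is a volume rather than a cost, and electricity lies outside the six, so the list is not shown to be closed. A data analysis plan is also announced. The named inputs and the all-costs perspective simply do not match, and the direction of any distortion depends on prices that are not given.
- **That cure rates will be similar, so a cure-only ratio is empty.** No expected cure difference is stated. The trial is described as a superiority trial, and favourable outcome at day 7 is a primary outcome.
- **That uncertainty intervals are missing.** These can be left to the announced analysis plan.

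**Conclusion.** The printed ratio is wrong as written: it is the reciprocal of the promised ICER, and its direction of preference is reversed. That rests on the article's text alone. The figures 0.004 and 250 are illustrations from assumed values.

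Two inconsistencies also hold on the text: cure alone in the ratio against cure plus antimicrobial prescription as the stated indicator, and test-delivery inputs that name no medicines against a perspective carrying all facility costs. The single contrast needs clarifying, since separate ratios per arm may be meant. The possible effect of medicines, from slight to a change of sign, depends on assumed unit prices and on which reading of the expected antibiotic reduction is taken.

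A reader might infer that the trial's main conclusions are at risk. They are not: randomization, sample size and the primary comparison do not depend on this formula. It is a specific, inexpensive correction to an ancillary analysis.

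**What to change.** In the economic section and its analysis plan:

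- Define ICER = (cost of algorithm − cost of comparator) / (effect of algorithm − effect of comparator).
- Calculate it for RDT-DA against routine, the e-algorithm against routine, and the e-algorithm against RDT-DA.
- Report cost per antimicrobial prescription averted alongside cost per additional cure. For the former, the effect difference is the comparator's prescription proportion minus the algorithm's, so that a reduction counts as positive.
- Add the cost of prescribed antimicrobials and of unscheduled visits to the named inputs. The article already has prescriptions and unscheduled visits recorded in the CRF. The record is of prescribing, so the costing should be described that way and not as medicines dispensed.

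The cost is obtaining unit prices for medicines and visits, plus a little more analysis. No further participants or trial procedures are needed.

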#### Conception of health economic survey

The objective of the health economics component is to estimate the cost-effectiveness ratio of the proposed algorithm compared to the detection practices in place in the health facilities of the Nanoro health district.

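### The formula printed for the incremental cost-effectiveness ratio is its reciprocal: extra cures per unit of extra cost, not cost per extra cure

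*Protocol article*

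**What the plan says.** Three places in the protocol article bear on this.

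- **Conception of health economic survey** gives the aim: to "estimate the cost-effectiveness ratio of the proposed algorithm compared to the detection practices in place".
- **Specific objectives** names the quantity and its use: "Calculate the incremental cost-effectiveness ratio;Determine the most cost-effective algorithm".
- **Methodology**, data analysis paragraph, sets the effect measure ("The healing rates of each algorithm will be estimated and will serve as an efficiency comparator") and then the ratio: "The incremental ratio will be calculated according to the following formula". The displayed fraction has proposed minus routine cure rate on top and proposed minus routine cost below.

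The trial has three arms: "1) control arm, (2) RDT decisional algorithm (RDT-DA) arm, and (3) e-algorithm arm". Two intervention arms can therefore each be compared with routine care. The article gives no unit for the ratio, no threshold, and no statement of whether a high or a low value is favourable. It says that an analysis plan for the economic data is still to be written.

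**The concern.** An incremental cost-effectiveness ratio is the extra cost divided by the extra effect. The article uses that name and then fixes a formula for the inverse. This is a definition that contradicts the document's own name for the quantity, not a detail left for later.

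The ratio feeds a decision, because the next listed objective is to say which algorithm is most cost-effective, and the article presents the trial as a possible route to a change of policy. A reader who meets a figure under this name will take it as money per extra cure and prefer the smaller value. Applied to the printed formula, that habit favours the arm that buys fewer cures per unit of money. A reader who sets the figure against a willingness to pay per cure compares numbers in different units.

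**Working it through.** **Inputs.** The article gives no costs, cure rates, ratio value or threshold, so it has no figure of its own to reproduce. All numbers below are assumed, with costs in arbitrary units per child.

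**Definitions.** Let dE be cure rate (proposed) minus cure rate (routine), and dC be cost (proposed) minus cost (routine).

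- Printed in Methodology: R = dE / dC
- Incremental cost-effectiveness ratio: ICER = dC / dE = 1 / R

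**Step 1: order of two arms that both cost more and cure more.** Routine care costs 2 and cures 93%. Option A costs 6 and cures 95%; option B costs 6 and cures 94%.

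| | dE | dC | printed R | ICER |
|---|---|---|---|---|
| A | 0.02 | 4 | 0.02/4 = 0.0050 | 4/0.02 = 200 |
| B | 0.01 | 4 | 0.01/4 = 0.0025 | 4/0.01 = 400 |

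A cures more at the same cost. The lower ICER selects A; the lower printed value selects B. The reversal is general when both differences are positive, because 1/x falls as x rises. A check on 100,000 assumed pairs (cure gain 0.01 to 0.10, extra cost 0.5 to 10) gave opposite choices in all of them.

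**Step 2: comparison with a willingness to pay.** Take A with dE 0.05 and dC 2, and B with dE 0.05 and dC 5. The ICERs are 40 and 100; the printed values are 0.025 and 0.010. At an assumed 50 units per cure, A is worth its cost (40 < 50) and B is not (100 > 50). Set directly against 50, both printed values look far below the limit. They have to be compared with 1/50 = 0.02 instead, and then give the right answer: 0.025 is above it and 0.010 below.

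**Step 3: is the arm with the lower printed value always the worse one?** No. Take A with dE 0.02 and dC 4, and B with dE 0.08 and dC 6. The printed values are 0.005 and 0.0133, so the lower one selects A. Net benefit is (value per cure × dE) − dC.

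- At 100 per cure: A = 2 − 4 = −2; B = 8 − 6 = 2. B is better, so the selection is wrong.
- At 20 per cure: A = 0.4 − 4 = −3.6; B = 1.6 − 6 = −4.4. A is the less unfavourable, so the selection is not wrong.

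Over assumed pairs at values of 20 to 500 per cure, the lower printed value selected the arm with the lower net benefit in about 80% to 93% of cases. Where one arm was both cheaper and more effective than the other, and both cost more and cured more than routine care, it selected the dominated arm every time.

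**Step 4: negative differences.** A number and its reciprocal have the same sign, so inversion does not alter the sign pattern. Suppose both arms save money.

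- Saving 3 each, cure +0.08 (A) and +0.04 (B): printed −0.027 and −0.013; ICER −37.5 and −75. A is better; the lower printed value selects A and the lower ICER selects B.
- Cure +0.05 each, saving 4 (A) and 2 (B): printed −0.0125 and −0.025; ICER −80 and −40. A is better; the lower printed value selects B and the lower ICER selects A.

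Neither form ranks reliably here.

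**The case against.** The strongest defence is that extra cures per unit of money is a legitimate quantity. Read with higher as better, it orders the options in Step 1 correctly, and with positive differences it can be compared with the reciprocal of a willingness to pay. The article never says that lower is better. This stands as a limit on the consequence. It does not remove the contradiction, since the article calls the quantity an incremental cost-effectiveness ratio and gives no label that would prompt the other reading.

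A second defence is that the formula describes one contrast, proposed against routine, so there are no two ratios to rank. The wording is indeed singular. But the trial has two intervention arms, and the stated objective is to find the most cost-effective option, so a comparison between them is a natural use.

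Third, a reader might infer that the inversion also gives wrong signs for dominant or dominated results, or that only the printed form breaks down near zero. Neither inference holds. The signs are identical in both forms. The printed ratio is unstable when the cost difference is near zero, and the conventional one when the cure difference is near zero. The latter is quite possible here, because the sample-size section quantifies a benefit in antibiotic prescribing and no gain in cure is quantified anywhere.

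Fourth, rules for dominance and for displaying uncertainty belong in the economic analysis plan still to be written, and their absence from an article is no fault. That is correct. They appear under the fix only because inverting the formula alone would leave the same ambiguity in place.

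**Conclusion.** The point holds as an error of definition: the printed formula is the reciprocal of the quantity the article says it will calculate. The contradiction rests on the text alone.

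Its consequence is conditional. The order of two algorithms is exactly reversed if the figure is read as cost per extra cure with lower preferred, and if both algorithms cost more and cure more than routine care. The first condition is customary but unwritten; the second depends on the data. A reader might go further and conclude that the plan will select the worse algorithm. The documents do not support that: they state no decision rule, and which arm is better can depend on the value placed on a cure (Step 3).

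The severity is moderate. The economic evaluation is ancillary, and the formula does not touch the primary or secondary outcomes, the sample size, randomisation or data collection. Costs and cure rates are estimated separately, so the conventional ratio can always be recovered (1/0.0050 = 200).

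**What to change.** In Methodology, replace the formula with

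(cost of proposed algorithm − cost of routine) / (cure rate of proposed algorithm − cure rate of routine)

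computed separately for the RDT-DA and e-algorithm arms, and state that the result is cost per additional cure. Carry the same definition into the economic analysis plan.

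Because either form is ambiguous in sign and unstable when its denominator is near zero, report each arm's cost difference and cure difference beside the ratio. Label a cheaper and more effective arm as dominant, and a dearer and less effective one as dominated, rather than giving those results as a bare number.

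The cost is one formula and a sentence or two of text. No additional data are needed and nothing else in the trial changes.
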